### Outcomes and data collection methods

All participants will be assessed at baseline, 6 and 12 weeks. The primary outcomes of this study are lumbar IVD T2, LBP intensity and disability. Secondary outcomes will examine IVD height and volume, paraspinal muscle volume and size, paraspinal and vertebral body fat fraction, feasibility, sleep quality, insomnia severity, health-related quality of life, inflammatory blood markers, habitual physical activity, recovery and treatment expectations, activity-specific beliefs, kinesiophobia, depression, anxiety and stress, pain catastrophising, pain self-efficacy and adverse events. Researchers processing and analysing MRI data will be blinded to group allocation. Given the participant is the outcome assessor for self-reported measures and the inability to blind group allocation, these outcomes will not be blinded. An overview of the data collection is available in table 2.

**Table 2 T2:** Overview of the study processes and data collection

	Enrolment	Allocation/baseline	6-week follow-up	12-week follow-up
	−t_1_	t_0_	t_1_	t_2_
Enrolment				
Eligibility screen	X			
Informed consent	X			
Allocation		X		
Interventions				
Intervention				
Waitlist				
Assessments				
Lumbar spine MRI		X	X	X
Pain intensity		X	X	X
Disability		X	X	X
Feasibility				
Sleep quality		X	X	X
Insomnia severity		X	X	X
Health-related quality of life		X	X	X
Inflammatory blood markers		X		X
Habitual physical activity		X	X	X
Past exercise history		X		
Recovery and treatment expectations		X	X	X
Activity-specific beliefs		X	X	X
Kinesiophobia		X	X	X
Depression, anxiety and stress		X	X	X
Pain catastrophising		X	X	X
Pain self-efficacy		X	X	X
Social support		X	X	X
Pressure pain thresholds		X		X
Exercise-induced hypoalgesia		X		X
Adverse events				
Participant feedback				X
Physical assessments		X		

#### Lumbar spine MRI

The morphology of IVDs,^12^ vertebral marrow fat^28^ and paraspinal muscles^12^ will be assessed via MRI at baseline, 6 weeks and 12 weeks using the following sequences: (1) T2 Sag spin-echo multiecho, (2) Sag mDIXON, (3) Axial mDIXON and (4) T2-weighted Sag. Each sequence will be completed using established and reliable methods.^12 28^ These sequences will enable the quantification of IVD composition, vertebral fat fraction and paraspinal muscle size and composition. To avoid the impact of diurnal variation,^29^ all scanning will be performed after at least 4 hours since waking and participants will be instructed not to perform any strenuous physical activity or sport on the day of scanning. Immediately before scanning, participants will be required to sit for 20 min. Blinded image tracing (ImageJ: https://imagej.nih.gov/ij/) and analysis will be performed for all MRI outcomes as in prior studies by the team^12 28^ to acquire the following:

IVD T2 (primary outcome)^12^: Individual lumbar IVD T2 (in ms) will be calculated by a linear fit of the natural logarithm of the image intensity across the eight echo times of the T2 Sag spin-echo multiecho sequence. IVD T2 will be calculated for the entire IVD and five equidistant subregions (anterior annulus, anterior nucleus, centre nucleus, posterior nucleus, posterior annulus).^14^ Lumbar IVD T2 has excellent test–retest reliability (ICC=0.98).^30^IVD height and volume^12^: Individual lumbar IVD height will be calculated from the T2 Sag spin-echo multiecho sequence. IVD volume will then be calculated by multiplying the area of each slice by the slice thickness and gap between slices.Nucleus–annulus signal intensity ratio^14^: T2-weighted Sag sequences will be used to determine the signal intensity of five equidistant subregions (anterior annulus, anterior nucleus, centre nucleus, posterior nucleus, posterior annulus) to calculate the nucleus–annulus signal intensity ratio.Paraspinal muscle volume and size^31^: Axial mDIXON sequences will be used to calculate muscle size and volume of the paraspinal muscles of multifidus, erector spinae, psoas major and quadratus lumborum. For these, we will primarily report on paraspinal cross-sectional muscle volume (cm^3^). Lumbar paraspinal muscle volume will be calculated by multiplying the area of each lumbar slice by the slice thickness plus the gap between slices. Lumbar level-specific average area (mm^2^) will also be calculated.Paraspinal muscle fat fraction^31^: Axial mDIXON sequences will be used to calculate the paraspinal fat fraction. The fat fraction will be calculated as 100%×signal intensity fat/(signal intensity fat+signal intensity water).Vertebral body fat fraction^28^: Sag mDIXON sequences will be used to calculate the vertebral body fat fraction. The fat fraction will be calculated as 100%×signal intensity fat/(signal intensity fat+signal intensity water).IVD to vertebral body height ratio^14^: Sag mDIXON sequences will be used to calculate the vertebral body height. This will then allow for calculating IVD height to vertebral body height ratio.Pfirrmann grading^32^: T2-weighted Sag sequences will be used to complete the radiographic grading of the IVDs using the Pfirrmann criteria.

#### Pain intensity

The visual analogue scale will quantify LBP intensity at baseline, 6 weeks and 12 weeks.^33^ The scale ranges from 0 to 100 points, with 0 considered no pain and 100 considered the worst pain imaginable. The primary measure will be the average pain intensity during the past week. We will also assess current pain intensity and worst pain over the last week as secondary measures. For adults with CLBP, a 20-point reduction will be considered the minimum clinically meaningful difference.^34^ The visual analogue scale has excellent test–retest reliability (ICC=0.90).^35^

#### Disability

The 10-item Oswestry Disability Index will quantify disability (poor physical function) due to LBP at baseline, 6 weeks and 12 weeks.^36^ Questions are rated from 0 to 5 points, with higher scores indicating greater disability. The total score from the questionnaire is doubled and represented on a 100-point scale. For adults with LBP, a 10-point reduction is considered the minimum clinically meaningful difference.^6^ The Oswestry Disability Index has good to excellent test–retest reliability (ICC=0.84–0.94).^36^

#### Feasibility

The following domains of feasibility will be documented throughout the study by members of the research team: recruitment ((1) enrolled participants compared with total screened potential participants, (2) reasons for ineligibility or declined participation, (3) enrolment timeline, (4) efficacy of recruitment pathways), attrition ((1) number of participants available for follow-up, (2) reasons for loss to follow-up), adherence ((1) overall training session attendance, (2) within-session training load completed), data collection ((1) missing data, (2) reasons for missing data), safety ((1) number of adverse events, (2) severity of adverse events), acceptability ((1) system usability survey). For feasibility purposes, additional pain intensity (visual analogue scale) measurements will be conducted at fortnightly intervals during the video consultation for the intervention group only.

#### Sleep quality

The 19-item Pittsburgh Sleep Quality Index will quantify sleep quality and duration over the previous month at baseline, 6 weeks and 12 weeks.^37^ The questionnaire assesses seven separate sleep components, including subjective sleep quality, sleep onset latency, sleep duration, sleep efficiency, sleep disturbances, use of sleep medication and daytime dysfunction. Each question results in a score from 0 to 3 points which are then summed to create a global score ranging from 0 to 21 points, whereby higher scores indicate poorer sleep quality. A global score of five points or greater indicates poor sleep quality.^37 38^ The Pittsburgh Quality Sleep Index has moderate to good test–retest reliability (ICC=0.70–0.86).^37^

#### Insomnia severity

The seven-item Insomnia Severity Index will be used to assess the nature, severity and impact of insomnia at baseline, 6 weeks and 12 weeks.^39^ The questionnaire evaluates the following insomnia dimensions: severity of sleep onset, sleep maintenance, early morning awakening problems, sleep dissatisfaction, interference of sleep difficulties with daytime functioning, noticeability of sleep problems by others and distress caused by sleep difficulties. The global score ranges from 0 to 28 points, whereby higher scores indicate higher severity of insomnia (0–7 points: absence of clinically significant insomnia; 8–14 points: subthreshold insomnia; 15–21 points: moderate insomnia; 22–28 points: severe insomnia). The Insomnia Severity Index has good test–retest reliability (ICC=0.84).^40^

#### Health-related quality of life

The six-item EQ-5D-5L will quantify the health-related quality of life at baseline, 6 weeks and 12 weeks.^41^ The questionnaire includes five dimensions: (1) mobility, (2) self-care, (3) usual activities, (4) pain/discomfort and (5) anxiety/depression. For each dimension, patients will identify either no, slight, moderate, severe or unable to/extreme problems. The questionnaire also includes a visual analogue scale spanning 0–100 points, which evaluates overall current health, with 0 considered the worst health one could imagine and 100 considered the best health one could imagine. A 10.5-point change is the minimum clinically meaningful difference in adults with LBP.^42^ The EQ-5D-5L has moderate to good test–retest reliability (ICC=0.73–0.84).^43^

#### Inflammatory blood markers

Within 7 days before measurements at baseline and between three and 7 days following the last exercise training session, participants will attend a commercial pathology clinic collection centre where a fasted morning (08:00–10:00) venous blood sample will be collected. Participants will be asked to refrain from eating or drinking anything aside from water 1 hour before the blood draw. Blood samples will be separated into serum/plasma by low-speed centrifugation (3000 rpm, 4°C for 10 min). Samples will be sent to a central pathology laboratory accredited by the National Association of Testing Authorities Royal College of Pathologists Australasia for testing of high-sensitivity C reactive protein (Melbourne Pathology) according to manufacturer instructions. The remaining samples will be stored in a −70°C freezer before being transferred to Deakin University, where samples will be stored at –80°C until analysis. Milliplex immunoassay kits (Millipore Corp, Billerica, USA) will measure markers associated with IVD health^44^: tumour necrosis factor alpha, interleukin 1 beta, interleukin 4, interleukin 6, interleukin 8, interleukin 12, interferon-gamma, as per the manufacturer’s recommendations. Prostaglandin E2 will be analysed by PGE2 Human ELISA Kit (Invitrogen, California, USA). Samples will be assessed in duplicate in a single batch after the study. A biological specimens’ statement is available in online supplemental appendix B.

#### Habitual physical activity

The seven-item International Physical Activity Questionnaire will quantify habitual physical activity at baseline, 6 weeks and 12 weeks.^45^ The questionnaire asks about the frequency/duration of vigorous and moderate intensity physical activity, walking and sitting over the past 7 days. Total weekly physical activity will be calculated by weighting each type of activity by its energy requirement in metabolic equivalent to produce a score in metabolic equivalent minutes. The International Physical Activity Questionnaire has moderate to excellent test–retest reliability (ICC=0.70–1.00).^45^

#### Past exercise history

The two-item Bone-specific Physical Activity Questionnaire will quantify physical activity levels by loading impact on bone.^46^ Given the rationale that IVD may similarly adapt to loading as bone, this questionnaire is relevant to the research questions in this study. The self-administered questionnaire quantifies physical activity at various ages from childhood to 12 months before the present. The second item quantifies physical activity in the last 12 months, including frequency each week. Participant responses are applied to a mathematical equation that generates a total bone-loading score, which considers ground reaction forces associated with each physical activity, frequency and years of participation. The questionnaire has been validated using accelerometery and measuring ground reaction forces in 19 physical activities.^46^

#### Recovery and treatment expectations

A three-item questionnaire will be used to assess general recovery expectations and expectations of treatment-specific benefit at baseline, 6 weeks and 12 weeks.^47–49^ To measure general recovery expectations by 6 and 12 weeks, responses are rated from 0 to 10 points, where 0 indicates no improvement and 10 indicates complete recovery. To measure treatment-specific expectations of the intervention, responses are rated from 0 to 10 points, where 0 indicates not at all helpful and 10 indicates extremely helpful.

#### Activity-specific beliefs

A six-item questionnaire will be used to assess the beliefs of safety towards specific physical activities at baseline, 6 weeks and 12 weeks. Questions one to four relate to the current and past involvement in a range of physical activities, while questions 5 and 6 evaluate the belief in safety. Question six asks the respondent, ‘Do you think the following exercises/movements are safe for you to do?’ Responses to 20 common physical activities are rated on a five-point Likert scale from definitely no to definitely yes. A 10–15 s video accompanies each activity to provide respondents with a clear reference. For activities perceived as unsafe (responses of definitely no and probably no), two additional questions will explore the meaning of this belief and the subsequent impact this has on participation.

#### Kinesiophobia

The 11-item Tampa Scale for Kinesiophobia will be used to quantify kinesiophobia at baseline, 6 and 12 weeks.^50^ Responses to questions relating to fear of movement, fear of physical activity and fear avoidance are rated on a four-point Likert scale from strongly disagree to strongly agree. Higher scores indicate greater levels of kinesiophobia. The Tampa Scale for Kinesiophobia demonstrates excellent test–retest reliability (ICC=0.91).^51^

#### Depression, anxiety and stress

The 21-item Depression Anxiety and Stress Scale will be used to measure depression, anxiety and stress at baseline, 6 and 12 weeks.^52 53^ Seven items on a four-point scale measure each factor of depression, anxiety and stress, where 0 indicates never and 3 indicates almost always. Scores range from 0 to 21 points on each subscale, with scores multiplied by two, and higher scores indicate greater levels of depression, anxiety and stress, with additional subscales for each construct. The Depression Anxiety and Stress Scale has good to excellent test–retest reliability (ICC=0.82–0.90).^52^

#### Pain catastrophising

The 13-item Pain Catastrophising Scale will measure pain catastrophising at baseline, 6 and 12 weeks.^54^ Responses are rated on a five-point scale, where 0 indicates not at all and 4 indicates all the time. Higher scores represent greater levels of pain catastrophising. The Pain Catastrophising Scale has good to excellent test–retest reliability (ICC=0.80–0.93).^54^

#### Pain self-efficacy

The 10-item Pain Self-efficacy Questionnaire will measure self-efficacy towards managing pain at baseline, 6 and 12 weeks.^55^ Responses are rated on a seven-point scale, where 0 indicates not confident at all and 6 indicates confident. Higher scores represent greater levels of pain self-efficacy. The Pain Self-Efficacy Questionnaire has excellent test–retest reliability (ICC=0.92).^56^

#### Social support

The 12-item Multidimensional Scale of Perceived Social Support will be used to measure perceived social support at baseline, 6 and 12 weeks.^57^ Responses are rated on a seven-point Likert scale and range from very strongly disagree to very strongly agree. Higher scores indicate greater levels of social support, with three subscales representing support from family, friends and significant others. The Multidimensional Scale of Perceived Social Support has good test–retest reliability (ICC=0.85).^58^

#### Pressure pain thresholds, exercise-induced hypoalgesia and expectations

Pressure pain thresholds will be used to examine hypersensitivity using a digital algometer (Commander Echo, J Tech Medical Industries, Salt Lake City, USA) at the forearm, paraspinals and calf using standard and reliable protocols at baseline and 12 weeks.^59 60^ Manual pressure will be applied using a 10 mm diameter rod at a rate of approximately 10 N/cm^2^ per second until the participant perceives the pressure as pain. The protocol will consist of two trials on each muscle region (left, right, left, right) before proceeding to the next region (ie, forearm, lumbar paraspinal, then calf) with 20 s rest between each trial. Test–retest reliability is excellent for pressure pain thresholds (ICC: wrist=0.81–0.97, leg=0.96–0.98, neck=0.92–0.98, back=0.94–0.99).^61^ Participants will receive neutral language instruction and complete familiarisation for one trial at each site following the procedures described above.^62^ To test endogenous analgesia (descending pain inhibition) in response to exercise, pressure pain thresholds will be reassessed following a 3 min isometric wall squat with feet at shoulder width and knee joint angle of 100 degrees using an established protocol.^59 63^ LBP intensity (visual analogue scale) will be evaluated immediately before and after the wall squat to determine a change in endogenous hypoalgesia. Participants will also record a rating of perceived exertion (6–20 points) following the exercise.^64^ Following pressure pain thresholds, participants will complete a two-item questionnaire to determine expectations of the wall squat on changes in pressure pain thresholds and LBP intensity.^62^

#### Adverse events

Participants will be instructed to inform the research team immediately should any adverse events occur. Moreover, participants allocated to exercise training will be asked about adverse events during a fortnightly video consultation (Zoom Video Communications, California, USA) with a study team member. Serious adverse events will be defined as any untoward medical occurrence that results in death, is life-threatening or requires hospitalisation. Non-serious adverse events will be defined as any other untoward medical occurrence. Adverse events will be classified as treatment-related if they are definitely or probably related to the exercise training intervention.

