## Abstract

Poor intervertebral disc (IVD) health is associated with low back pain (LBP). This 12-week parallel randomised controlled trial will evaluate the efficacy of a progressive interval running programme on IVD health and other clinical outcomes in adults with chronic LBP. Participants will be randomised to either a digitally delivered progressive interval running programme or waitlist control. Participants randomised to the running programme will receive three individually tailored 30 min community-based sessions per week over 12 weeks. The waitlist control will undergo no formal intervention. All participants will be assessed at baseline, 6 and 12 weeks. Primary outcomes are IVD health (lumbar IVD T2 via MRI), average LBP intensity over the prior week (100-point visual analogue scale) and disability (Oswestry Disability Index). Secondary outcomes include a range of clinical measures. All outcomes will be analysed using linear mixed models. This study has received ethical approval from the Deakin University Human Research Ethics Committee (ID: 2022-162). All participants will provide informed written consent before participation. Regardless of the results, the findings of this study will be disseminated, and anonymised data will be shared via an online repository. This will be the first study to evaluate whether a progressive interval running programme can improve IVD health in adults with chronic LBP. Identifying conservative options to improve IVD health in this susceptible population group has the potential to markedly reduce the burden of disease. This study was registered via the Australian New Zealand Clinical Trials Registry on 29 September 2022 (ACTRN12622001276741).

WHAT IS ALREADY KNOWN ON THIS TOPICExercise training is known to improve a range of health-related outcomes (eg, pain intensity and disability) in adults with chronic low back pain.WHAT THIS STUDY ADDSThis randomised controlled trial will be the first to examine the safety and efficacy of a progressive interval running programme on intervertebral disc (IVD) health.HOW THIS STUDY MIGHT AFFECT RESEARCH, PRACTICE OR POLICYThis study represents a critical step towards identifying a conservative treatment capable of improving IVD health in this susceptible population group.

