### Interventions

#### Exercise training

The exercise training will consist of three community-based 30 min sessions per week for 12 weeks prescribed by an accredited exercise physiologist from the research team. Exercise training sessions will be individualised based on information during a 30 min initial assessment completed at Imaging @ Olympic Park. Exercise training sessions will consist of a 5 min general warm up followed by an interval-based running programme that will be progressed weekly as guided by an accredited exercise physiologist from the research team. The programme for each participant will be delivered and monitored through the RunKeeper application (ASICS Runner App, Boston, USA), using a preallocated study code allowing for deidentified tracking of running speed, distance and surface (ie, grass, gravel, paved, trail or mixed). Participants will receive educational content delivered via REDCap throughout the intervention covering the following topics: (a) ideal running speed, (b) footwear selection, (c) the safety of running and (d) dealing with setbacks (online supplemental appendix A). Participants will initially meet for 15 min weekly (weeks 1–4) and then fortnightly (weeks 6–12) via secure video consultation (Zoom Video Communications, California, USA) with a member of the study team to discuss the exercise training programme.

10.1136/bmjsem-2022-001524.supp1Supplementary data

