#### Waitlist control

Participants allocated to the waitlist control arm will be asked to manage their LBP per usual (eg, general practitioner management, over-the-counter pharmacotherapy) and avoid commencing a running programme. No formal intervention will be provided during the 12-week follow-up. Following completion of the study, waitlist participants will be offered the same exercise training programme and one-on-one consultation with an accredited exercise physiologist as per the intervention group.

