### Participant timeline

Recruitment commenced on 3 October 2022 and will continue until 40 participants are enrolled. All participants will attend face-to-face data collection at baseline, 6 and 12 weeks post baseline (figure 1). Participants allocated to exercise training will commence the week of baseline data collection and continue until 12-week postbaseline data collection.

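### Direct questioning about adverse events is stated for the running arm only, so any between-arm comparison of event counts would be tilted towards more recorded events with running

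*Protocol article*

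**What the plan says.** The Adverse events section sets one rule for everybody: "Participants will be instructed to inform the research team immediately should any adverse events occur". It then adds a second route for one arm: "participants allocated to exercise training will be asked about adverse events during a fortnightly video consultation".

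The consultations are described under Exercise training: "Participants will initially meet for 15 min weekly (weeks 1–4) and then fortnightly (weeks 6–12) via secure video consultation". The waitlist arm has no such contacts. Its section says "No formal intervention will be provided during the 12-week follow-up". Both arms do share study visits: "All participants will attend face-to-face data collection at baseline, 6 and 12 weeks post baseline". No adverse event question is described for those visits.

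Adverse events close the list of secondary outcomes in Outcomes and data collection methods ("pain catastrophising, pain self-efficacy and adverse events"). They also appear under Feasibility as "safety ((1) number of adverse events, (2) severity of adverse events". The summary box after the Abstract says the trial "will be the first to examine the safety and efficacy of a progressive interval running programme".

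**The concern.** How many non-serious events are recorded depends on how often, and how directly, people are asked. The protocol's definition of a non-serious event is broad: any untoward medical occurrence that is not serious. It therefore takes in minor complaints that a participant may not think to report unprompted. The Exercise training section itself notes daily pain fluctuation in up to 35% of people with chronic low back pain, so some background of flares is to be expected in both arms.

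The waitlist arm is the trial's only guide to that background. If its events come in by self-report alone while the running arm is also questioned, part of any excess in the running arm may reflect the questioning and not the running. The stakes are a misleading safety message, in which the programme looks less safe than it is. Analysis cannot repair this afterwards, because waitlist events that were never elicited are not in the data.

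**Working it through.** The documents give no adverse event rate, no capture rate and no planned figure for this outcome, so there is nothing of the plan's own to reproduce. The check has two parts.

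**1. Number of direct enquiries per arm.** The Adverse events section speaks of a fortnightly consultation. The Exercise training section has weekly consultations in weeks 1–4 and fortnightly ones in weeks 6–12. Three readings are possible:

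| Reading | Weeks with an enquiry | Running arm | Waitlist (stated) |
|---|---|---|---|
| Asked at every consultation | 1, 2, 3, 4, 6, 8, 10, 12 | 8 | 0 |
| Asked fortnightly through all 12 weeks | 2, 4, 6, 8, 10, 12 | 6 | 0 |
| Asked only in the fortnightly phase | 6, 8, 10, 12 | 4 | 0 |

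The contrast with the waitlist arm holds on every reading.

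**2. Illustration of the direction and possible scale.** Inputs:

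- Participants per arm: 20 (Sample size section).
- True risk of at least one event, the same in both arms: 20%, 40% or 60% (assumed).
- Capture with direct questioning plus self-report: 0.9 (assumed).
- Capture with self-report alone: 0.3, 0.5 or 0.7 (assumed).

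Expected participants with a recorded event = 20 × true risk × capture. The recorded risk ratio is the ratio of the two capture values, so it does not depend on the true risk: 0.9/0.3 = 3.00, 0.9/0.5 = 1.80 and 0.9/0.7 = 1.29.

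| True risk, both arms | Running (capture 0.9) | Waitlist, capture 0.3 | Waitlist, capture 0.5 | Waitlist, capture 0.7 |
|---|---|---|---|---|
| 20% | 3.6 | 1.2 | 2.0 | 2.8 |
| 40% | 7.2 | 2.4 | 4.0 | 5.6 |
| 60% | 10.8 | 3.6 | 6.0 | 8.4 |

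For example, at 40% true risk and self-report capture of 0.5: 20 × 0.40 × 0.9 = 7.2 against 20 × 0.40 × 0.5 = 4.0. That is an apparent risk difference of 0.36 − 0.20 = 0.16 where the true difference is zero. Over the whole grid the spurious risk difference runs from 0.04 (20% risk, capture 0.7) to 0.36 (60% risk, capture 0.3). With equal capture in both arms (0.9 and 0.9) the expected risk ratio is 1.00 and the difference is 0.

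Only the direction comes from the protocol. The scale comes from the assumed capture values.

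**The case against.** The strongest reply is that the protocol writes out no between-arm test of adverse events. It places their number and severity under feasibility, and it classifies relatedness to the exercise intervention only. The safety of the programme can then be described within the running arm, whose counts the unequal questioning does not affect. This stands as far as it goes. A reader might infer from the Abstract's statement that all outcomes go into linear mixed models, and from the between-group wording in Statistical methods, that a formal comparison of event counts is planned. That generic wording is weak evidence, since event counts have no baseline from which to model change. But adverse events are a listed secondary outcome of a randomised two-arm trial, and readers will set the arms side by side whether or not a test is run.

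Second, a reader might infer that waitlist events go uncollected, or that nobody asks about them at 6 and 12 weeks. The documents do not support that. Self-report applies to both arms. The empty adverse event row in Table 2 proves nothing, because rows for activities that plainly take place are empty too, and a condensed article may omit visit-level forms. What the text does support is extra enquiry in one arm and no stated equivalent in the other.

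Third, back pain and disability are measured identically in both arms at baseline, 6 and 12 weeks, including worst pain over the last week. It would therefore be too strong to say that an excess of back pain flares in the running arm could not be interpreted at all. Those measures miss flares outside their recall windows and do not cover other injuries. Serious events, which involve death, threat to life or hospitalisation, are also the least likely to go unreported without a prompt.

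Fourth, the bias makes running look less safe, so it does not give false reassurance. That limits the harm but does not make the comparison sound.

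**Conclusion.** The point holds in a limited form. As written, adverse events are collected more intensively in the running arm (4 to 8 direct enquiries) than in the waitlist arm (self-report only, as far as the article states). Any between-arm comparison of counts, chiefly of non-serious events, would be biased towards more recorded events with running. This assumes that direct questioning picks up events that self-report misses, and that the waitlist arm has no equivalent enquiry in a fuller document that is not shown.

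The size is unknown. The risk ratios of 1.29 to 3.00 illustrate assumed capture values and are not estimates for this trial. Nor do the documents show that the waitlist rate will in fact be too low to serve as background: they give no rate, and only the direction of the error follows from the design. Running-arm counts alone remain valid description. The point is worth acting on because the correction is cheap and fits existing visits.

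**What to change.** Put the same adverse event questions to both arms in the existing 6- and 12-week online questionnaires, with recall since the last visit. State that any between-arm comparison will use only those answers. Keep the consultation enquiries as they are for participant safety, and report the events found there as descriptive data for the running arm only. Reconcile the Adverse events and Exercise training sections so that it is clear which consultations include the question. If the waitlist arm is already asked at study visits, say so in the Adverse events section.

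The cost is two extra questionnaire items and a minor ethics amendment, communicated through the registry as the Protocol amendments section provides. No extra visits or staff are needed. Participants already past week 6 when the change is made will have less comparable data. Some bias will remain, because running participants may better recall events they have already discussed at a consultation, and minor events may be forgotten over a six-week recall period.
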